Health services for PEH frequently focus on crisis-based medical, nursing and addiction services, often with a gender-blind lens [18, 19]. High levels of stigma, shame and fear result in women accessing services even less and seeking help at breaking point with complex coinciding physical and mental health needs [20, 21]. Homelessness and substance use in women is inter-sectoral and may overlap with trauma, abuse, domestic and sexual violence and exploitation, and the needs of these women are complex and unique [22]. Pathways into homelessness are frequently different to that of men and require a different approach [23]. Internationally, gender-based services for women who are experiencing homelessness and addiction are lacking and services are mostly delivered in mixed gender settings [18, 19]. Women-specific services are recommended to increase safety, stability, wellbeing, and psychosocial functioning to respond meaningfully to the serious health and social care needs of women in this setting [24]. Gender specific and gender sensitive research is required to fill this knowledge gap [25].

Our prior research, the LEAP-I study demonstrated high retention (83% female v 42% males) with excellent engagement and feedback from its female participants, yet caution was observed around engaging in a mixed exercised programme with men [16]. Women have traditionally been underserved in research and policy, yet multiple sources cite women as the fastest growing homeless demographic [23]. No study has examined how targeted women-only exercise programmes with nutritional supplementation work in practice in this population.

The overall aim of this study is to evaluate the feasibility and impact of exercise with protein supplementation, delivered with a low threshold and trauma informed approach, on physical functioning and frailty outcomes in a group of (non-geriatric) women experiencing homelessness and addiction challenges, through the delivery of an exercise intervention, followed by qualitative interviews. The objectives are:

To evaluate recruitment, retention and adherence rates, and any adverse effects of the intervention.To evaluate pre- and post-intervention levels of physical function, nutritional and frailty status, pain, and general health status.To evaluate programme feedback and gain deeper insights into participants perspectives and experiences of the exercise intervention.

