## Materials and methods

### Study design, setting and time frame

This single-arm quantitatively driven, sequential mixed-methods feasibility study will take place in Jane’s Place, Merchants Quay Ireland (MQI), a five day per week drop-in day-service centre in Dublin city centre, which provides medical and support services for socially excluded women who are homeless and/or in addiction. Following the intervention qualitative research in the form of individual exit interviews will be conducted with 20 participants. This study has received ethical approval from the Faculty of Health Sciences, Trinity College Dublin on Jan 18^th^ 2024 (Ethical Approval Reference Number: 211202).

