The intervention will be delivered by two research physiotherapists who will adhere to all safety procedures. Flexibility will be facilitated with the provision of a four-week window for pre-intervention evaluations prior to commencement of the programme. Using a trauma-informed lens [46] flexibly arranged group or one-to one sessions will be delivered based on participant preference. Exercise programming strategies and variables are based on our earlier work (LEAP-I and LEAP-II trials) [16, 17] and also informed by prior stakeholder involvement from people with lived experience. The exercise classes will be multi-modal, with a primary focus on strength and based on core set of resistance exercises (Table 3). Aerobic, balance and flexibility work will be integrated into the class and the exercises will be individualised based on initial assessment results and presentation of participants. Using a gender-based perspective, the following considerations and adaptions will be built into the class; (i) core-stability exercises to target pelvic floor and/or abdominal muscle weakness, (ii) bone building exercises to target peri-and postmenopausal bone loss and (iii) age-associated muscle mass loss. Music, dance and fun orientated physical activity games, an important feature of aforementioned linked studies, will be incorporated to optimize enjoyment and self-esteem. These features are incorporated to offer choice and enable empowerment in respect of a trauma informed approach, while carefully considering the exercise prescription parameters outlined above [45]. Borg’s Rate of Perceived Exertion Scale will be used to monitor effort and scale the intensity of the workout [47]. To promote post-exercise muscle protein synthesis, a nutritional supplement (200ml pre-prepared ‘protein shake’, Fresubin) which consists of 20g of protein will be offered immediately post exercise. The ‘Park Walk’ will focus on the aerobic component of the intervention, using open green space to maximise physical and mental health outcomes. It will be a flexibly arranged 20–30-minute self-paced group or one-to-one walk. To build sustainability beyond the ten-week programme brief health promoting and physical activity educational interventions will be included in the exercise class setting to empower people to engage in unsupervised exercise following the study. As per routine procedure in the centre, which incorporates frequent reminders regarding upcoming appointments or events, phone messages will be incorporated to remind participants of the weekly schedule.

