#### Sample size

A sample size calculation was conducted on the statistical package R, based on an expected adherence of 60%, a minimal acceptable adherence of 45% and a power of 80%, which indicated that a target sample size of 68 would be required. Due to the novelty of this study, the challenges of recruitment in this ‘hard to reach’ population and the feasibility focus of this study, while 68 will be the recruitment target, a minimal of 24 will be sought [53].

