## Data collection and management

### Analytic plan

All data will be pseudonymised at point of entry into excel spreadsheets and then transferred into IBM SPSS V28 for analysis. For quantitative data, nominal or ordinal variables will be reported as frequencies and percentages. Continuous variables will be summarised as mean and standard deviation if normally distributed and median and inter-quartile range if non-normally distributed. Data will be tested for normality using the Kolmogorov–Smirnov/Shapiro Wilk test and will be compared across timepoints using the general linear model procedure (normally distributed data) and the Friedman’s test (non-normally distributed data). Chi-squared t-tests will be used where appropriate and some data may be categorised to investigate relationships between variables. Exploratory regression models will be developed to explore correlates and predictors of frailty and poor physical functioning. For the qualitative data, Braun and Clarke thematic analysis methodology will be employed to provide an in-depth analysis of the exit interview data [50]. A *p*-value of <0.05 will be considered significant. To account for multiple comparisons, we will apply a Bonferroni correction by dividing the significance level by the number of tests conducted.

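### With only a pre and a post assessment described, Friedman's test reduces to the sign test; the signed-rank test is usually the more efficient choice for continuous outcomes that prove non-normal

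*Protocol article*

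**What the plan says.** The second objective in the Introduction is "To evaluate pre- and post-intervention levels of physical function, nutritional and frailty status, pain, and general health status". The Intervention section mentions "provision of a four-week window for pre-intervention evaluations prior to commencement of the programme", which is one baseline assessment spread over a window. The text describes no mid-programme or later follow-up assessment. The SPIRIT figure, which might show a schedule, is not reproduced in the copy reviewed.

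Under Study design the trial is "This single-arm quantitatively driven, sequential mixed-methods feasibility study", so any comparison of outcomes over time is within the same woman. The Analytic plan says that outcomes "will be compared across timepoints using the general linear model procedure (normally distributed data") "and the Friedman’s test (non-normally distributed data"). It names no other paired test for two timepoints. It adds: "Chi-squared t-tests will be used where appropriate and some data may be categorised to investigate relationships between variables". The threshold is a p-"value of <0.05 will be considered significant", with a Bonferroni correction for the number of tests.

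**The concern.** Friedman's test is designed for three or more related measurements. With two, ranking within each woman gives only a 1 and a 2, so the test knows who improved and who worsened but not by how much. A woman who gains one second of single leg stance counts the same as one who gains twenty. This is a stated choice of test, not a detail left for a later document.

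At stake is power on the secondary outcomes. With a single arm, the pre-post comparison is the main quantitative evidence on impact. The minimum recruitment is 24 women, the analysed pairs may be fewer after dropout, and Bonferroni tightens the threshold further. Giving away information on the size of change may therefore cost findings that the same data could support.

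**Working it through.** **The plan's own figure.** The protocol gives no power figure for this comparison. Its one calculation, under Sample size, is "based on an expected adherence of 60%, a minimal acceptable adherence of 45% and a power of 80"%, giving 68. It reproduces as a one-sample proportion at one-sided 5%:

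n = [(1.645·√(0.45·0.55) + 0.842·√(0.60·0.40)) / 0.15]² = [(0.818 + 0.412) / 0.15]² ≈ 67.3, so 68.

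This concerns adherence and does not depend on the test for secondary outcomes.

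**The identity.** Let n₊ women improve and n₋ worsen. With two timepoints Friedman's statistic is

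Q = (n₊ − n₋)² / (n₊ + n₋), on 1 df,

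which is the sign-test chi-square. Zero changes drop out under the tie correction. Numerical check:
- 24 women, 14 up and 10 down: (14 − 10)²/24 = 0.667; computed Friedman 0.667.
- 68 women, 42 up and 26 down: (42 − 26)²/68 = 3.765; computed Friedman 3.765.

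**Power for normal changes.** The effect sizes are assumptions, in SD of the paired differences; the protocol gives none. The level is two-sided 5% before Bonferroni. The Friedman side is exact binomial arithmetic:
- n = 24, shift 0.6 SD. P(improve) = Φ(0.6) = 0.726. Reject when |2k − 24| > √(24·3.841) = 9.60, that is k ≥ 17 or k ≤ 7. Power 67% (simulation 68%). Signed-rank, by simulation: 78%.
- n = 68, shift 0.4 SD. P(improve) = Φ(0.4) = 0.655. Reject when |2k − 68| > √(68·3.841) = 16.16, that is k ≥ 43 or k ≤ 25. Power 70% (simulation 71%). Signed-rank: 89%.

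With no change, these Friedman rules reject 6.4% of the time at n = 24 and 3.8% at n = 68. The n = 24 figure therefore slightly flatters Friedman. At an illustrative Bonferroni level of 0.005 with n = 68 and 0.4 SD, power is 42% against 63%.

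**Other shapes of change (Friedman against signed-rank, simulated, assumed distributions).**

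| Setting | n = 24 | n = 68 |
|---|---|---|
| Skewed raw scores before and after | 45% v 49% | 80% v 91% |
| Heavy-tailed t(3) changes (0.5 SD at 24; 0.3 SD at 68) | 85% v 85% | 84% v 91% |
| Laplace changes (0.5 SD at 24; 0.3 SD at 68) | 78% v 75% | 80% v 81% |

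For skewed raw scores the gain is thus about 4 to 11 points.

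**Coarse ordinal scores.**
- Changes of −1/0/+1 with probabilities 12/45/43%, n = 24: 55% v 55%. All non-zero ranks tie, so the two statistics coincide.
- Changes from −2 to +2 with probabilities 2/12/45/33/8%: 43% v 44% at n = 24 and 80% v 78% at n = 56.
- Rounded normal changes, SD 1, shift 0.5, n = 24: 55% v 60%.

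**Level of the signed-rank test.** If there is no pre-post effect and the two scores are exchangeable, the differences are symmetric and the test keeps its level. If the differences are skewed (gamma) with a median of exactly zero, it rejects about 8% at n = 24 and 16% at n = 68. Read as a test of the median change, it needs rough symmetry.

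**The case against.** Four objections deserve weight.

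1. The number of timepoints is inferred. The Analytic plan says only that data are compared across timepoints, and the figure that might show a schedule is missing from the copy reviewed. With a third assessment Friedman would be a proper choice. This stands as a condition, but everything in the text points to two.
2. The gain is smallest where it might be expected to matter most. The Clinical Frailty Scale, the pain rating and the nutrition score are integer scales with many ties, and on such scales the two tests are close. The signed-rank test also treats steps on an ordinal scale as comparable in size, so a direction-only test is defensible there. Clearly normal data go to the general linear model, so the normal-change figures are not the typical case for Friedman. All this stands, and it narrows the point to continuous outcomes that prove non-normal.
3. A reader might infer a much larger loss from skewed changes, such as 55% against 82% (24 women, 0.6 SD). That figure depends on the direction and centring of the skew. With mean-centred lognormal changes skewed the other way the sign test wins, so the figure is not relied on.
4. A reader might infer that a chi-squared test of independence will be applied to frailty or nutrition categories before and after in the same women. The text does not say this. It says the tests are used where appropriate, in a sentence about relationships between variables, and the odd test name reads as a dropped word. Only a wording correction follows.

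**Conclusion.** The point holds in a limited form. On the two assessments described, Friedman's test is the sign test exactly, and it discards the size of change. It would be wrong to conclude that the planned test is invalid, or that real improvements across the battery will be missed; the documents support only that it is usually less efficient for some outcomes.

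For continuous measures the signed-rank gain is about 11 points (78 − 67) to 19 points (89 − 70) in the two normal-change cases worked above, smaller at n = 24 for skewed scores, and nil or slightly negative for some heavy-tailed changes. These sizes rest on assumed effects and distributions, on two-sided 5% before Bonferroni, and on 24 or 68 complete pairs. Priority is low, because the primary outcome is feasibility and the sample size rests on adherence.

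**What to change.** In the Analytic plan, for non-normal outcomes measured at two timepoints:
- Name the Wilcoxon signed-rank test on the paired differences, with the Hodges-Lehmann estimate of change and its 95% CI.
- State that normality is checked on the paired differences, not on the raw scores.
- Keep the sign test for outcomes whose changes are clearly asymmetric.
- Keep Friedman's test only if the schedule contains a third assessment, and then for the overall comparison.
- Correct the chi-squared wording to name the tests intended. Specify a paired test (McNemar or marginal homogeneity) for any pre-post comparison of categories within the same women.

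The cost is a sentence or two of text, and no extra data are needed. The one statistical downside is the signed-rank test's need for roughly symmetric differences when read as a test of the median, which the retained sign test covers.

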**2. Physical performance and lower extremity physical function**:

This will be measured using the following physical performance measures:

The 10m Walk Test (10mWT). This test measures gait speed and functional mobility and is recorded in m/s. Gait speed is calculated as total distance/time [31].The 2 Minute Walk Test (2MWT). This test of self-paced walking ability and functional capacity assesses a participants’ ability to walk unaided over a 15m distance, as fast as possible, for two minutes. Rest breaks are permitted, and the distance covered is measured [30].The Chair Stand Test (CST). This tests lower limb strength and endurance and records the total number of sit to stand repetitions performed in 30 seconds [29].The Single Leg Stance Test (SLST). This balance test is performed on each leg. The participant is timed standing unassisted on one leg, with eyes open and hands placed on the hips [31].

**3. Frailty:** Frailty will be assessed using the Clinical Frailty Scale (CFS) [6] and the SHARE-Frailty Instrument (FI) [33]. The CFS is validated for people over 65 years. It is assessed by the tester. Each point on the scale correlates with a level of frailty and a visual chart aids classification from 1 (very fit) to 9 (terminally ill). Higher scores indicate higher levels of frailty. The SHARE-FI is validated for people over 50 years [33]. It consists of four brief questions related to the following variables: exhaustion, loss of appetite, walking difficulties and low physical activity, and grip strength measurement. The five results are entered into a freely available web calculator to generate a frailty score and a frailty category of non-frail, pre-frail and frail is also generated. A minor modification was made to the terminology of the SHARE-FI to reflect the real-world experiences of this population.

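### The analytic plan allows full-scale measures to be categorised for association tests; wherever that is done, an exploratory analysis of 24 to 68 women loses power it could keep at almost no cost

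*Protocol article*

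**What the plan says.** The Analytic plan section of the protocol article states: "Chi-squared t-tests will be used where appropriate and some data may be categorised to investigate relationships between variables". It names no variables and no cut-points. The next sentence adds: "Exploratory regression models will be developed to explore correlates and predictors of frailty and poor physical functioning". It does not say whether outcomes and predictors in those models keep their full scale.

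The same section sets the threshold ("A *p*-value of <0.05 will be considered significant") and the multiplicity rule: "we will apply a Bonferroni correction by dividing the significance level by the number of tests conducted". The number of tests is not given.

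Under Secondary outcomes, gait speed is in m/s, the 2-minute walk is a distance, the chair stand is a count and single leg stance is a time. Grip and limb circumferences are measured quantities. MNA-SF, the pain rating and SF-12 are scores. For SHARE-FI, a web calculator is used to "generate a frailty score and a frailty category of non-frail, pre-frail and frail is also generated", so both forms are available. Cut-offs and reference values are cited there for comparing participants' results, not for testing associations.

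On size, the Sample size section says that "while 68 will be the recruitment target, a minimal of 24 will be sought".

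**The concern.** The article names categorisation as a way of studying relationships between variables and sets it beside chi-squared tests. Cutting a measured variable into groups treats everyone on one side of the cut as equal. That discards information, and the result then depends on where the cut falls. With 24 to 68 women there is little information to spare, and every additional test also lowers the Bonferroni threshold for all the others.

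What is at stake is the exploratory search for correlates of frailty and poor physical function. A real relationship could be missed in a cross-table that the uncut data would have shown, and the empty table could be read as evidence of no relationship. The Discussion expects the findings to guide clinicians and policy makers, so an avoidable false null has some cost.

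The sentence is also garbled. It joins the chi-squared test and the t-test into one name, so it needs rewriting in any case.

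**Working it through.** **1. What the sample was sized for.** Inputs from Sample size: minimal acceptable adherence p0 = 0.45, expected adherence p1 = 0.60, power 80%. Alpha and sidedness are not stated there; one-sided 5% is tried first.

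n = [z(0.95)·√(p0·q0) + z(0.80)·√(p1·q1)]² / (p1 − p0)²
= [1.645 × 0.4975 + 0.842 × 0.4899]² / 0.15²
= 1.514 / 0.0225 = 67.3, so 68.

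The stated 68 reproduces with a one-sided 5% test; a two-sided test needs 86. The sample was therefore sized on one proportion, not on relationships between variables.

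**2. Information kept after a cut.** For a bivariate normal pair and small correlations, a median split of one variable keeps 2/π = 64% of the information. Splitting both keeps (2/π)² = 41%.

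**3. Sample size needed for 80% power at an assumed r = 0.4, two-sided 5%** (1.960 + 0.842 = 2.802):
- Full scale: (2.802 / atanh 0.4)² + 3 = about 47.
- One split: the correlation falls to 0.4 × √(2/π) = 0.319, and (2.802 / atanh 0.319)² + 3 = about 75.
- Both split: phi = (2/π)·arcsin 0.4 = 0.262, and (2.802 / 0.262)² = about 114.

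The target of 68 is enough in the first case only.

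**4. Power at the planned sizes.** Simulation of bivariate-normal samples, at least 20,000 per setting, two-sided 5%. Full scale is the Pearson test. One split compares means across a median split. Both split is an uncorrected 2×2 chi-squared test with cuts at the sample medians.

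| n | r (assumed) | Full scale | One split | Both split |
|---|---|---|---|---|
| 24 | 0.3 | 29% | 19% | 12% |
| 24 | 0.4 | 51% | 33% | 21% |
| 24 | 0.5 | 73% | 50% | 32% |
| 68 | 0.3 | 71% | 51% | 27% |
| 68 | 0.4 | 93% | 77% | 49% |
| 68 | 0.5 | 99% | 94% | 72% |

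Repeat runs agree to about one percentage point.

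**5. Why the double-split figure is a range.** Cutting at the population medians gives 35% (n = 68, r = 0.3), 57% (n = 68, r = 0.4) and 27% (n = 24, r = 0.4). With sample medians at n = 68, all margins are 34 and each expected cell is 17. A cell 4 above expectation gives chi-squared = 68 × (4/17)² = 3.76, just short of 3.84; 5 above gives 5.88. This coarse step makes the test conservative.

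**6. Rank correlation.** If Spearman replaces Pearson, power at n = 68 and r = 0.3 is 65% to 66% instead of 71%, still above the 51% with one split.

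**7. Under the Bonferroni rule.** With 10 tests assumed (0.05/10 = 0.005), n = 68 and r = 0.4, power is 73% on the full scale, about 45% with one split and 26% to 30% with both.

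**The case against.** The strongest reply is that the sentence is conditional. It says that some data may be categorised and that the tests apply where appropriate; it does not say that gait speed, grip or the SHARE-FI score will be cut. A reader might infer that the plan categorises its measures as a rule and that the study therefore loses much of its power. The text does not support this. Continuous variables are summarised by mean or median, changes over time go to a general linear model or Friedman's test, and correlates of frailty and function are assigned to regression models, which can use the full scale. This stands.

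Chi-squared tests also have natural uses here. Most of the demographic variables are categorical, such as living arrangement, marital status and history of incarceration. Table 1 defines the attendance groups in advance. For those variables the test is suitable, and the concern does not extend to attendance as Table 1 defines it. This stands too.

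Two further strong readings fail. One is that real correlates would usually be missed: at n = 68 and r = 0.4, one split still leaves 77% power, and at n = 24 and r = 0.3 even the full scale reaches only 29%, so sample size is the main limit there. The other is that cut-points would be chosen after seeing the data. The article does not say so, and naming cut-points is detail commonly left to a statistical analysis plan.

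The objection does not remove the point itself. Categorisation is named as a method for studying relationships, without limit, and the regression sentence does not commit to the full scale. That is a choice stated in the article, not a detail left out.

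**Conclusion.** The point holds in conditional form, as an inexpensive improvement. The article permits measured quantities and scores to be cut for association tests, gives no reason for it, and leaves open whether the regression models avoid it.

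At r = 0.4, two-sided 5%, cutting one variable costs 16 points of power at n = 68 (93 − 77) and 18 at n = 24 (51 − 33). Cutting both costs 36 to 44 points at n = 68 (93 − 57, 93 − 49) and 24 to 30 at n = 24 (51 − 27, 51 − 21). The cost is only 5 points for one split at n = 68 and r = 0.5 (99 − 94).

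The sizes rest on assumptions that the article does not supply: the correlations, bivariate normality (approximate at best for bounded scores), median splits and, for the Bonferroni case, 10 tests. The direction of the loss does not depend on the particular correlation chosen.

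The analyses affected are exploratory and secondary. The primary feasibility outcome and the adherence-based sample size are untouched.

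**What to change.** Replace the categorisation sentence in the Analytic plan with:

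*Relationships between variables will be investigated with measured quantities and scores on their original scale (Spearman or Pearson correlation, and linear or ordinal regression in the planned exploratory models). Chi-squared or Fisher's exact tests will be limited to variables that are categorical by definition, such as living arrangement, menopausal status and the attendance groups of Table 1. Categories of measured variables, such as SHARE-FI class or values below a reference cut-off, will be used for description only.*

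This also removes the garbled test name. Comparing a measured quantity between two natural groups remains possible: linear regression on one binary predictor is the equal-variance t-test.

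The cost is one sentence, with no new data and no extra participants. The downside is that correlations and slopes are less familiar to service staff than tables of proportions. Those tables can still be shown descriptively.
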